### Variables to be measured

#### Demographic information.

In the baseline survey, we will administer a demographic survey that asks patients to answer questions about age, sex at birth, gender identity, race/ethnicity, health insurance status, type of cancer and age at cancer diagnosis, zip code of primary residence, sexual orientation, living situation and employment status. These will not be asked at follow-up.

#### Consent, Randomization, concealment of allocation, and blinding.

Interested potential participants will schedule a telephone call with the research coordinator to learn more about the study. After confirming study eligibility and sharing consent information, the research coordinator will obtain the participant’s verbal informed consent to participate in the study. Following verbal consent, participants will be sent an electronic survey via REDCap to review the full electronic consent information form and then subsequently complete the baseline survey. Participants will be required to review the electronic consent information form prior to initiating the baseline line survey. If participants prefer to, they may elect to complete the baseline survey over the phone with the research coordinator. Participants will be considered enrolled in the study upon completion of the baseline survey. After enrollment, a research coordinator responsible for enrollment and study operations but not involved in data collection or analysis will randomize them in a 1:1 ratio to either Enhanced Social Prescribing intervention or enhanced usual care using random permutated blocks [43]. Randomization will be conducted using REDCap. Procedures to ensure allocation concealment include using parallel structures in REDcap for each arm, which reduces the possibility that study personnel interacting with the database can infer treatment assignment.

Enrollment and study coordination staff will not be blinded, as they will be responsible for configuring the randomization scheme in REDCap and assigning participants to study arms following a review of the electronic consent information and completion of the Baseline survey. Because of the nature of the intervention and enhanced usual care, participants will not be blinded to treatment arm. To reduce risk of bias in assessing primary and secondary outcomes, the biostatistician and analyst conducting analyses will remain blinded to treatment assignment until primary outcome analysis results are complete. Outcome data will be collected using electronic surveys administered via REDCap. A team member not involved in enrollment and randomization will conduct any follow-up calls to collect outcome data from individuals without email or who do not complete the outcome electronic survey. The study biostatistician and analyst will remain blinded by being restricted from accessing the randomization dashboard and associated forms within the REDCap project. We do not anticipate any circumstances in which the biostatistician or analyst would need to be unblinded.

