**Fig 2 pone.0350956.g002:**
[figure not shown]
Study consort flow diagram.

We will collect the outcome measures from patients at 9 and 17 weeks after enrollment via REDCap survey. The research coordinator will conduct additional outreach, including telephone, text message, email, and written communication according to each participants’ preference to ensure complete data collection. Participants will receive USD 25 for completing each outcome assessment. Participants will be analyzed using an intent to treat analysis and included in primary outcomes analysis even if baseline data are missing. Missing data will be described to assess the amount, patterns, and reasons for missigness. Any variable with substantial missigness will undergo careful review before being considered as a candidate variable for future trials.

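### Allocation concealment is not secured as described, because the role that enrolls also configures the randomization scheme, and the coordinator's outcome outreach is not kept apart from the rule on who makes outcome calls

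*Protocol article*

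**What the plan says.** All references are to the protocol article. Most of the relevant text is in *Consent, Randomization, concealment of allocation, and blinding*.

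- **Eligibility and consent:** "After confirming study eligibility and sharing consent information, the research coordinator will obtain the participant’s verbal informed consent".
- **Randomization:** once the baseline survey is complete, "a research coordinator responsible for enrollment and study operations but not involved in data collection or analysis will randomize them", in REDCap, "using random permutated blocks". No block size is given, and the article does not say whether sizes vary.
- **Set-up of the scheme:** "Enrollment and study coordination staff will not be blinded, as they will be responsible for configuring the randomization scheme in REDCap". The same sentence also gives these staff the assignment of participants to arms.
- **Concealment:** "Procedures to ensure allocation concealment include using parallel structures in REDcap for each arm". The stated purpose is to make it harder for personnel working in the database to infer which arm someone is in.
- **Outcome calls:** "A team member not involved in enrollment and randomization will conduct any follow-up calls to collect outcome data", for people who have no email or do not complete the electronic survey.

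*Data collection and data management* then covers the 9- and 17-week surveys: "The research coordinator will conduct additional outreach, including telephone, text message, email, and written communication". The aim given there is complete data collection.

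**The concern.** Concealment requires that whoever decides that a person is eligible, and when that person enters, cannot foresee the next assignment. Here the role that makes those decisions also sets up the scheme. The measure offered as concealment works on assignments that already exist, so it supports blinding of database users and leaves the next assignment unprotected.

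There is some room to act on foreknowledge. The coordinator contacts people to schedule the call at which eligibility is formally confirmed (*Recruitment*). Some exclusions call for judgement, such as moderate or severe cognitive impairment or active psychosis (*Characteristics of participants and eligibility criteria*). Selective entry or timing could then make the arms differ for reasons other than chance.

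The second issue is outcome follow-up. The primary outcome is self-reported loneliness, and participants know their arm. If a coordinator who also knows the arm administers the survey by telephone, answers could shift by arm.

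The estimates from this pilot are to set the sample size of the full trial (*Sample size calculation*), and its procedures are meant to carry over to that trial (*Abstract*, Discussion). A weak allocation procedure would carry over with them.

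**Working it through.** The plan states no figure on this point, so there is none to reproduce. The check sets the statements side by side and then sizes the foreseeability under stated assumptions.

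**1. Who does what before assignment**

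| Task | Role named |
|---|---|
| Schedules the call, confirms eligibility, takes consent | Research coordinator |
| Randomizes | A research coordinator responsible for enrollment |
| Configures the scheme and assigns arms | Enrollment and study coordination staff, unblinded |
| Generates or holds the sequence independently | No one named |

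The first three rows are one staff group. The text describes no separation between setting up the scheme and enrolling.

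**2. What the named measure protects**

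Parallel structures make the records of the two arms look alike, so a database user cannot easily tell the arm of someone already randomized. The next row of the allocation table, or the arms left in the current block, are unaffected.

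**3. How foreseeable assignments are in permuted blocks**

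Inputs: 36 participants and 1:1 permuted blocks (from the article). Assumptions: one sequence, a fixed block size of 2k, and an enroller who knows the size and all earlier assignments.

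An assignment is certain once one arm is used up within the block. The certain assignments are therefore the final run of a single arm. The expected number of A's after the last B is k/(k+1), and the same holds for B's after the last A. The expected number certain per block is 2k/(k+1). Dividing by 2k gives a share of 1/(k+1).

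By hand for size 4, the six orders AABB, ABAB, ABBA, BBAA, BABA and BAAB have 2, 1, 1, 2, 1 and 1 certain assignments. The mean is 8/6 = 4/3 per block, and (4/3)/4 = 1/3.

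Enumerating every block of each size gives:

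| Block size | Share certain | Of 36 | Best guess correct |
|---|---|---|---|
| 2 | 1/2 = 50% | 18 | 75% |
| 4 | 1/3 = 33% | 12 | 71% |
| 6 | 1/4 = 25% | 9 | 68% |
| 8 | 1/5 = 20% | 7.2 | 67% |

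The last column guesses whichever arm has more places left in the block; guessing by chance would be right 50% of the time. Size 8 does not divide 36 evenly, so 7.2 is simply the share applied to 36.

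**4. Who contacts participants for outcomes**

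The blinding section says that the randomizing coordinator takes no part in data collection, and it reserves outcome-collecting calls for someone outside enrollment and randomization. The data collection section gives the research coordinator outreach that includes the telephone, with complete outcome data as its purpose. It neither limits the outreach to reminders nor refers back to the reserved role. Staff working from that section alone could make the calls that the other section assigns elsewhere.

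**The case against.** The strongest reply is that configuring a scheme is not the same as seeing the list. The article does not say that enrolling staff generate the sequence or can view the table. Assignment is made in REDCap after the baseline survey is complete. The concealment measures are introduced as including parallel structures, so the list is not presented as exhaustive. The full protocol is a supplement that is not shown, and it may settle block sizes and user rights. A reader might infer that allocation is unconcealed, or that staff know every upcoming assignment. The documents support neither. They do support the narrower point, because the overlap of roles and the mislabelled measure are stated in the text and are not omissions.

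The block figures are conditional. They need fixed blocks and an enroller who tracks past assignments, and they illustrate a risk without measuring a defect in this trial. Room for selection is also limited, because screening is self-completed with a numeric loneliness cut-off.

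On follow-up, the outreach can be read as reminders only, which would fit with the reserved calls. Three further inferences should be resisted:

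- Baseline by telephone with the coordinator comes before randomization, so it cannot bias answers by assigned arm. At most it sits awkwardly with the statement that the coordinator does not collect data.
- The article never calls the outcome caller blinded, only uninvolved in enrollment and randomization.
- One and the same person is not established. The text speaks of a research coordinator, and there may be several.

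Finally, the study is not powered for effectiveness, and none of the progression criteria in Table 1 is a between-arm comparison. That lowers the severity but does not remove the point.

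**Conclusion.** The concern holds in a limited form. As described, one staff role both enrolls and configures the scheme, and the one measure named does not hide the next assignment, so concealment is not secured. How many assignments could be foreseen depends on details the article does not give. Under fixed blocks of 2 to 8, with the size and history known, between a fifth and a half would be certain in advance. With varying block sizes and no access to the table, the problem would be much smaller.

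The follow-up wording is a failure to separate two duties, not a proven breach. Any effect would be confined to participants whose outcomes are collected by telephone, since most outcome data come from electronic self-report.

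This should be fixed, but it does not call the feasibility decision into question. It matters for the between-arm estimates and for the procedure handed on to the larger trial.

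**What to change.** 1. **Sequence.** For participants not yet randomized, have an existing team member or a REDCap administrator without participant contact generate and upload the allocation table, with varying block sizes. Enrollment has begun, so start the new table only after any open block is completed, to avoid breaking balance within it.
2. **User rights.** Remove set-up and table-viewing rights from enrolling staff. Leave them only the right to randomize once baseline is complete.
3. **Wording on concealment.** State who generates and holds the sequence, and describe the parallel structures as protecting the blinding of the analysts and other database users.
4. **Follow-up.** In *Data collection and data management*, limit the coordinator to reminders, and assign all telephone-administered 9- and 17-week surveys to the team member already named in the blinding section.

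The cost is a small amount of REDCap user-rights work, a few sentences of text, and one modification to the ethics board, to which *Trial governance* says protocol changes are submitted. Assignments already made, and those left in an open block, cannot be protected retrospectively. The documents say only that the institute hosts REDCap, so whether its staff could do the upload has to be confirmed.

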#### Recruitment.

We will use a multimodal recruitment strategy in partnership with the two health systems (n = 3 primary care clinics) that is well established by our research group [44,45]. One clinic is located in Washington state and one clinic is in the Northwest region, but outside of Washington state. The strategies include flyers, provider referrals, and/or electronic health record (EHR) query. We will use our patient advisory groups to help inform strategies for recruitment within these recruitment strategies.

**Provider referrals**: Prior to the beginning of the trial, the study PI will give a presentation to providers and staff at participating clinics during a regularly scheduled staff meeting (or another meeting as preferred by the clinic staff) on the study, eligibility criteria and intervention. Providers will be given flyers that include a link, QR code, and telephone number to the study interest form, to inform patients about the study. Providers will be able to hand out these flyers to patients. Interested patients will then be directed to either access the interest form electronically and complete it independently or reach out to the study coordinator by phone, email and/or text if they have any questions.

**EHR query and outreach**: We will provide parameters information to participating clinics that will conduct EHR queries to identify adult (age 18 or older) patients with a history of cancer (ICD-10 C00-D49). The research team will partner with the clinic to send information about the research study via email, mail or patient portal to eligible patients. The communication will instruct interested patients to complete the interest form electronically.

After patients complete the interest form, they will be directed to complete a brief screening questionnaire to assess eligibility. Patients will be given USD 15 for completing the screening questionnaire form. The screening questionnaire includes the 3-item UCLA Loneliness Scale and demographic questions and patient responses will determine study eligibility. Upon completion of the screening questionnaire, a research coordinator will contact the participant to schedule the initial study phone call for formal eligibility confirmation, consent, and distribution of electronic baseline enrollment survey.

We will continue the recruitment strategies above until we reach our goal of 36 participants enrolled. Participants will be allocated to one of two study arms of roughly equivalent size. Recruitment for this study opened on 15/03/2026 and will last for six months (14/09/2026) or until recruitment target (n = 36) is reached, whichever comes first.

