### Trial status and timeline

This study protocol is registered at clinicaltrials.gov (NCT07418437). As of March 2026, we have begun enrollment of participants. Full enrollment is anticipated by 9/30/2026. All data collection is anticipated to be completed by 12/31/26. Results of primary outcomes analysis is expected by 3/31/2027. The timeline of study data collection is provided in Supplement 3.

Prior to the feasibility study, we engaged adult cancer survivors to collaboratively adapt an intervention, building on the social prescribing model and using the ADAPT-ITT framework [36]. The Enhanced Social Prescribing intervention builds on the social prescribing model and also includes psychosocial educational support and is delivered in a group setting.

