### Sample size calculation

Because this is a feasibility pilot study, no sample size calculations were performed. 36 participants was selected as an enrollment goal based on ensuring sufficient enrollment for at least two cohorts for the enhanced social prescribing intervention and matching enrollment to the available resources and timeline. The estimates of baseline and outcome measures from this study will be used to calculate sample size for a full-scale trial.

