## Outcomes

### Assessment of trial feasibility

#### Research procedures feasibility.

Research procedures feasibility outcomes include number of individuals screened, number of individuals enrolled, time to first enrollment, time to reach enrollment milestones (25% target enrollment, 50% target enrollment, 75% target enrollment, 100% target enrollment), completeness of baseline and follow-up data, rate of participant drop-out or withdrawal, and the proportions of participants randomized to enhanced social prescribing that attended each scheduled session. Progression criteria for feasibility assessment are shown in Table 1.

**Table 1 pone.0350956.t001:** Progression criteria for feasibility assessment.

	Green	Yellow	Red
50% Enrollment	3 months	6 months	9 + months
Baseline data collection	100%	90%	50% or less
Drop out	<1	1-2 participants	N/A*
Intervention delivery	75% of participants	60% of participants	<60% of participants

• If greater than 2 participant drop outs are noted during the course of the study, the team will undertake full review of the study protocol and procedures to identify and mitigate design features that may be contributing to drop out.

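### Table 1's progression thresholds do not fit the trial's own recruitment window, so a recruitment shortfall, or three or more drop-outs, receives no colour

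*Protocol article*

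**What the plan says.** Table 1 (Outcomes, Research procedures feasibility) gives colour-coded progression criteria in four rows:

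- Time to 50% enrolment: Green 3 months, Yellow 6 months, Red 9 or more months.
- Baseline data collection: Green 100%, Yellow 90%, Red 50% or less.
- Drop-out: Green fewer than 1, Yellow 1 to 2 participants, Red marked not applicable. A footnote requires a full review of protocol and procedures if more than 2 participants drop out.
- Intervention delivery: Green 75%, Yellow 60%, Red below 60% of participants.

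The Recruitment section contains two stopping rules. One is open-ended: "We will continue the recruitment strategies above until we reach our goal of 36 participants enrolled". The other is dated: "Recruitment for this study opened on 15/03/2026 and will last for six months (14/09/2026) or until recruitment target" of 36 is reached, whichever comes first. Trial status and timeline adds "Full enrollment is anticipated by 9/30/2026" and "All data collection is anticipated to be completed by 12/31/26", with primary results expected by 31/03/2027.

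The section on consent and randomisation states: "Participants will be considered enrolled in the study upon completion of the baseline survey". Verbal consent comes before that survey and randomisation after it.

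Two retention figures stand outside Table 1. Implementation (Statistical analyses) requires at least 90% of participants to complete all data collection points. Expected findings (Discussion) anticipates at least 70%.

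**The concern.** Assessing the feasibility of a larger trial is a stated primary goal, and Table 1 is the only colour-coded rule for judging it. Such a rule should give a verdict for every result the pilot can produce, above all for poor ones. Read against the recruitment dates and the definition of enrolment, the table does not. The clearest recruitment failure, closing with less than half the target, falls in no cell. A fairly ordinary number of drop-outs also falls in no cell. The baseline row can be read so that it carries no information. If these levels are settled only after the results are known, the progression decision becomes post hoc.

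**Working it through.** **Enrolment row**

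1. The plan's own figure: 15/03/2026 to 14/09/2026, both days included, is 184 days; 184 / 30.4375 = 6.0 months. The stated six months is reproduced.
2. The milestone is 50% of 36 = 18 participants.
3. Nine months from opening is 15/12/2026. From 14/09/2026 to 15/12/2026 is 92 days, so Red begins about three months after recruitment closes.
4. A recruitment rate that reaches 18 at nine months is 18 / 9 = 2 per month. At closure that gives 2 × 6 = 12 enrolled. Such a pilot never observes the milestone and has passed the six-month Yellow level. The same holds for any final count from 0 to 17.
5. Under the open-ended rule, a participant enrolled on 15/12/2026 reaches week 17 (119 days later) on 13/04/2027. That is after the end of data collection on 31/12/2026 and after the results date of 31/03/2027. Red is therefore outside the stated timeline on either rule.
6. The timeline is tight already. Seventeen weeks from 14/09/2026 is 11/01/2027, and the last enrolment date compatible with 31/12/2026 is 03/09/2026.

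**Drop-out row**

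1. The last coloured level is 2 participants. Three or more has a review but no colour.
2. The documents give no expected drop-out rate, so a range is assumed. With X ~ Binomial(36, p), the chance of leaving the coloured levels is P(X ≥ 3):

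| Assumed p | P(X ≥ 3) |
|---|---|
| 5% | 0.27 |
| 10% | 0.71 |
| 15% | 0.92 |
| 20% | 0.98 |

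3. The 90% benchmark: 0.90 × 36 = 32.4, so 33 must complete and 3 may fail to.
4. The 70% expectation: 0.70 × 36 = 25.2, so 26 must complete and 10 may fail to.
5. If failing to complete the data points counts as drop-out, both figures accept results beyond the last coloured level in Table 1.

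**Baseline row**

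1. Denominator enrolled: enrolment is completion of the survey, so survey completion is 100% by definition. Only item-level gaps can lower it.
2. Denominator consented: Red is possible. With 36 enrolled, it needs at least 36 / 0.50 = 72 consented. The 90% level corresponds to 36 / 0.90 = 40 consented. From 41 consented (36 / 41 = 87.8%) to 71 consented (36 / 71 = 50.7%) there is no colour.

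**Delivery row, for comparison**

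Red is reachable: 10 of 18 is 55.6%, and 11 of 18 is 61.1%.

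**The case against.** A reader might infer that three of the four rows cannot return Red, and that a failed pilot would therefore give no warning. The documents do not support that.

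- **Baseline.** Table 1 states no denominator. The feasibility outcomes list "completeness of baseline and follow-up data", and Data collection and data management says participants will be "included in primary outcomes analysis even if baseline data are missing". The authors plainly allow for incomplete baseline data, and among consented people Red can occur. The row is undefined; it has not been shown to be incapable of Red.
- **Drop-out.** The footnote is an explicit escalation once more than two participants drop out. Its stated aim is to find and mitigate design problems, so it does not say whether to progress, but it is a signal.
- **Follow-up.** The 90% benchmark sits outside Table 1 but exists. A pilot that enrolled 10 and lost 4 would have 6 / 10 = 60% complete, which fails that benchmark and would also trigger the footnote review.
- **Enrolment.** The open-ended stopping rule, read alone, would let a nine-month milestone occur. Numbers enrolled and times to milestones will be reported in any case, so a shortfall would be visible, and a team could choose to read a milestone never reached as Red.

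All four points limit the problem. None supplies the missing colour: the table does not say how to classify fewer than 18 at closure, and the dated rule and the timeline both exclude nine months.

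**Conclusion.** The point holds for the fit between Table 1 and the rest of the protocol. The enrolment Red lies 92 days beyond the recruitment close, and any final enrolment of 0 to 17 is unclassified. Three or more drop-outs is also unclassified. At assumed drop-out rates of 5% to 20% that result has a probability of 0.27 to 0.98, on the assumption of independent drop-out among 36 participants. The comparison with the 90% and 70% figures assumes that not completing the data points counts as drop-out, which the protocol does not define. The baseline row is informative only among consented participants or at item level, and it has an uncoloured band from just above 50% to just below 90%.

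A reader might also infer a minimum of 24 participants, enough for two intervention groups of six at 1:1 allocation, from the sample size rationale of "ensuring sufficient enrollment for at least two cohorts for the enhanced social prescribing intervention". That text explains the enrolment goal of 36. It is not a progression criterion and does not support a further threshold.

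Feasibility is analysed descriptively and no treatment comparison is biased. What is affected is the progression decision.

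**What to change.** 1. **Enrolment row.** Restate it within the six-month window. Green: 18 or more by 3 months. Yellow: 18 reached after 3 months and by recruitment close. Red: fewer than 18 at close.
2. **Recruitment rules.** Reconcile the open-ended and the dated stopping rule, and align the result with the 30/09/2026 enrolment date and the 31/12/2026 end of data collection.
3. **Drop-out row.** Give more than two drop-outs a progression colour and keep the footnote review beside it. Define drop-out, and set cut-offs consistent with a single follow-up completeness criterion that replaces the present 90% and 70%.
4. **Baseline row.** State that the denominator is consented participants. If item-level completeness is of interest, report it separately.
5. **Bands.** Write each as a range so that every possible value has one colour.

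The cost is rewording one table and a few sentences, submitted as a protocol modification. No new data are needed. The team must choose the drop-out and follow-up cut-offs, and should do so before the feasibility results are known. The pilot could then return Red for recruitment or drop-out, which is the purpose of the table.
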